### Measures

#### Electroencephalography

Participants will undergo a 21-channel EEG measurement with Nexus-32 hardware and Biotrace+ software (Mind Media BV). The EEG will be collected from 19 standard 10/20 positions [44] and the right and left mastoid with a sampling rate of 512 samples per second. The left mastoid will serve as the online reference. Flat type electrodes will be placed above and below the left eye and at the outer canthi of each eye to correct for vertical and horizontal eye movements. Participants will be seated comfortably while 5 minutes of eyes closed resting state EEG data is collected. EEG measures will be conducted at T0 and T1 as well as at 12 months follow-up for participants in the intervention group (T2).

For participants in the neurofeedback group, a 1-minute baseline recording over 3 conditions will be conducted before start of the first neurofeedback session and after the last session. EEG signal will be recorded from electrode position Cz against a right ear mastoid reference across the conditions (1) eyes open, (2) eyes closed, and (3) cognitive task (where participants are instructed to solve simple mathematical calculations). These measurements will be used to determine neurofeedback threshold values and to assess change in mean magnitude of frequency bands before and after neurofeedback training.

#### Barratt Impulsivity Scale–11

The Dutch version of the BIS-11 (eleventh edition) [45] is a self-report questionnaire designed to measure the behavioral and personality construct of impulsivity across 3 second-order factors: attentional, motor, and nonplanning. It consists of 30 items scored on a 4-point scale ranging from rarely/never to almost always/always. The BIS-11 has been proven to be an internally consistent measure of impulsivity among inmate populations [45].

#### Cued Go/No-Go Task

The cued go/no-go task is a continuous performance test measuring impulse control by the ability to inhibit prepotent responses [40]. Participants are instructed to respond to a green square by pressing a button as quickly as possible while not responding to a blue square. A go or no-go cue is given before the actual target appears, providing information about the likelihood of an actual go or no-go target [40]. The likelihood of a correct target after a cue is manipulated with a 80/20 ratio, with 80% being a correct cue and 20% being an incorrect cue. Cues are presented with 4 fixed stimulus onset asynchronies (100, 200, 300, and 400 ms), giving participants time to prepare for responding. The cued go/no-go task has been proven to be a useful measurement of impulse control in substance abusing populations [40]. It consists of 250 trials spread over 5 rounds with a 30-second break between each round, taking approximately 20 minutes to complete. Outcome measurements are omission (the participant does not respond when he should respond) and commission errors (the participant responds when he should not respond) and reaction time.

#### Modified Desire for Alcohol Questionnaire

The DAQ-SF [46] is a self-report questionnaire assessing the desire to use drugs at the moment of assessment. It is derived from the original desire for alcohol questionnaire (DAQ) with 36 items. The short-form version of the DAQ consists of 14 item that can be scored on a scale from 1 to 7 ranging from strongly disagree to strongly agree. It consists of 3 factors: (1) strong desires/intention to drink, (2) negative reinforcement, and (3) ability to control drinking. The abbreviated version has been shown to be reliable in measuring alcohol craving [46].

All questions of the original questionnaire are designed to measure craving purely for alcohol; however, within the treatment facility alcohol use is less common than other drug use (such as marijuana and/or cocaine). Therefore, questions from the questionnaire have been altered so they can fit any type of drug dependency. An example of this is “My desire to drink seems overpowering” which has been altered to “My desire to use drugs seems overpowering.”

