
### Objectives

Primary outcome variables are the degree of impulsivity as measured with the Dutch version of the BIS-11 [39]; inhibitory control as measured with a cued go/no-go reaction time task [40]; degree of drug craving as measured with an altered version of the Desire for Alcohol Questionnaire (DAQ) [41]; actual drug use as measured with urine, saliva, or breathalyzer analysis; and changes in resting state EEG pattern.

Primary objective: To what extent does a reduction in impulsivity by using SMR-neurofeedback result in a reduction of core symptoms of SUD such as craving and actual drug use in a population of forensic psychiatric patients with a diagnosis of SUD?

Secondary objectives:

1. To what extent can an SMR-based neurofeedback intervention reduce levels of impulsivity as measured by BIS-11 and a cued go/no-go task in a population of forensic psychiatric patients with a diagnosis of SUD?

2. To what extent can an SMR-based neurofeedback intervention reduce levels of craving as measured by self-report questionnaire DAQ-SF (short form) in a population of forensic psychiatric patients with a diagnosis of SUD?

3. To what extent can an SMR-based neurofeedback intervention reduce actual drug use as measured with urine, saliva, or breathalyzer analysis in a population of forensic psychiatric patients diagnosed with SUD?

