### Participants

A power analysis calculation for the RCT using G*Power 3 (Department of Psychology) based on a 1-tailed alpha value of .05, a power value of 0.80, and an effect size (*f*) of 0.80 yielded a recommended sample size of 21 participants each in the control and intervention conditions. Given the special research population we aim to select 25 participants for each condition.

Participants are male patients diagnosed with SUD (substance dependency or substance abuse) according to the *Diagnostic and Statistical Manual of Mental Disorders*, Fourth Edition, Text Review (DSM-IV-TR [43]) and currently staying at the treatment facility. Participants have tested positive for drug use in the past 24 months at time of inclusion. Drug use is operationalized as urine, saliva, or breathalyzer analysis testing positive for either marijuana and/or psychostimulant/opioid drugs and/or alcohol. Corresponding with treatment facility policy, nonprescribed medication that is used for recreational drug consumption such as inhaled methylphenidate will also be scored as positive drug testing, as will refusal to undergo drug testing.

Participants are allowed to continue using prescription medication (as prescribed by a psychiatrist or general physician of the treatment facility) but are required to inform researchers of any medication they are currently using or any change in medication during treatment with neurofeedback.

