#### Actual Drug Use

Drug testing is performed on a regular basis, usually once every 2 weeks. Whenever staff suspects illegal use of substances within 2 moments of drug testing, spontaneous and unexpected drug testing can be performed. Number of drug tests will be counted, as will be positive (meaning drug use in the period of time since last drug test) and negative (meaning no drug use since last testing) outcome scores. Drug testing is done in the form of urine, saliva, or breathalyzer (for alcohol use only) analysis.

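### Men can enter the trial on an alcohol test alone, but the altered craving item shown names only drugs, so alcohol craving may be under-reported on a primary outcome

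*Protocol article*

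**What the plan says.** **Who enters.** Under Participants, the Protocol article requires a substance use disorder and a recent positive test: "Participants have tested positive for drug use in the past 24 months at time of inclusion". A test counts when it is "testing positive for either marijuana and/or psychostimulant/opioid drugs and/or alcohol". The final alternative means that alcohol on its own is enough.

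**How use is measured.** Under Actual Drug Use: "Drug testing is done in the form of urine, saliva, or breathalyzer (for alcohol use only) analysis". Alcohol therefore also counts in the drug-use outcome.

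**How craving is measured.** Objectives lists as a primary outcome the "degree of drug craving as measured with an altered version of the Desire for Alcohol Questionnaire". The section on the modified questionnaire explains that the original items concern alcohol only, that drinking is less common in the facility than other drug use, and that "questions from the questionnaire have been altered so they can fit any type of drug dependency". One of the 14 items is shown before and after the change: "My desire to drink seems overpowering" became "My desire to use drugs seems overpowering". The only reliability evidence cited is for alcohol craving.

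**The concern.** The questionnaire was altered because it covered alcohol and nothing else. The one edit shown replaces the reference to drinking instead of adding to it, so it risks leaving the opposite gap. A man whose problem is alcohol may read the item as being about other substances and disagree with it before and after treatment, whatever his craving for drink.

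This matters for three reasons:

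- Craving is a primary outcome and is central to the primary objective, which runs from impulsivity to craving and use. If some men answer the craving items for drugs only while their tests include alcohol, the two outcomes cover different substances for those men.
- Unregistered change in some men would pull the group-by-time effect on craving towards zero.
- The n-of-1 series uses the same scale twice a week. It approaches first the men with the highest outcome scores at T1, and it makes the second treatment period depend on significant improvement in the end points. Under-reported alcohol craving could affect both steps.

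**Working it through.** **Step 1. The texts side by side.**

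| Element | Place in the Protocol article | Is alcohol named? |
|---|---|---|
| Entry test | Participants | Yes, and sufficient alone |
| Drug-use outcome | Actual Drug Use | Yes, by breathalyzer |
| Aim of the altered scale | Modified Desire for Alcohol Questionnaire | Any drug dependency; alcohol not singled out |
| Altered item as shown | Same section | No |

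Alcohol is explicit wherever the investigators define or test for use. It is not explicit in the one text shown that a patient reads.

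**Step 2. Reproduce the planned sample size, to have a reference effect.** Inputs from Participants: one-tailed alpha 0.05, power 0.80, effect size 0.80, result 21 per arm.

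- Normal approximation: n = 2(1.645 + 0.842)² / 0.80² = 19.3, so 20 per arm.
- Exact two-sample t-test with d = 0.80, one-sided: 20.03, so 21 per arm. This matches the plan.

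The article labels the effect size *f*. A true *f* of 0.80 corresponds to d = 1.60 and needs only 6 per arm, so the planning value is in effect d = 0.80. The calculation is not tied to a named outcome; I apply it to craving for illustration only.

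**Step 3. Dilution.** Let p be the share of men whose change in craving the scale does not register. The documents give no value for p, so 0% to 30% is an assumed range. Suppose that p is the same in both arms, that the other men show the full effect, and that the SD is unchanged. The standardised difference is then

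d(p) = 0.80 × (1 − p).

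Power comes from the one-sided t-test at alpha 0.05 with 25 per arm (48 degrees of freedom) and noncentrality d(p) × √(25/2).

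| Assumed p | Men per arm (25 × p) | d(p) | Power, 25 per arm | n per arm for 80% power |
|---|---|---|---|---|
| 0% | 0 | 0.80 | 87% | 21 |
| 5% | 1.25 | 0.76 | 84% | 23 |
| 10% | 2.5 | 0.72 | 81% | 25 |
| 20% | 5 | 0.64 | 72% | 31 |
| 30% | 7.5 | 0.56 | 62% | 41 |

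Raising the target from 21 to 25 per arm absorbs a share of up to about 10%, if no men are lost for other reasons. Above that, power for craving falls below 80%.

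**The case against.** The strongest reply is that alcohol is a drug in the protocol's own vocabulary. It falls within the operational definition of drug use, the breathalyzer is described under drug testing, and the questionnaire section contrasts alcohol with other drug use. A reader might infer from the separate mention of alcohol in the entry criterion that the protocol does not regard it as a drug. That does not follow: marijuana is also listed separately there, and the questionnaire section plainly treats it as a drug. This part of the reply stands. The article does not contradict itself on what counts as drug use. The remaining question is whether patients, who answer the printed item, share that usage.

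Second, the article prints one item of 14, in English, for a Dutch facility, and shows no instructions to patients. A briefing that drugs include alcohol may exist. This also stands. If it does exist, the sponsor need only confirm it, and the point largely closes.

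Third, a reader might infer that alcohol patients score at the bottom of the scale and cannot change. The documents do not support that. It would require every such man to read drugs as excluding alcohol and to crave nothing else, and the items on ability to control use need not sit at the floor at all. Nor does entry on an alcohol test make a man an alcohol-only patient.

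Fourth, a reader might infer that a switch from drugs to drink would pass as benefit. On the craving scale alone it might. But actual use is also a primary outcome and includes alcohol tests, so such a switch can appear there.

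**Conclusion.** The concern holds as a mismatch of coverage. The trial admits men on alcohol alone and counts alcohol as use, yet the altered craving item it shows does not name alcohol. Some men whose problem substance is alcohol may therefore under-report craving, and the craving effect may be diluted. This is a risk created by the wording shown, not a demonstrated loss of data.

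Its size cannot be derived from the documents, which say only that alcohol use is less common. The loss of power from about 87% to 62% is an illustration over the assumed 0% to 30% range and rests on the conditions stated with the calculation. If the share is about 10% or less, the planned 25 per arm still gives about 80% power or more. The point is worth acting on because craving is a primary outcome and the remedy is small.

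**What to change.** Make alcohol explicit for every item of the altered questionnaire. Either reword the items, for example *use drugs (including alcohol)*, or print a standard instruction that drugs include alcohol. Use the same text at T0, T1 and T2 and throughout the n-of-1 series. If such an instruction is already in use, state it in the protocol.

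A wording that keeps one generic term and states that it includes alcohol is preferable to joining two separate questions in each item, which would make the items double-barrelled.

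If data have already been collected without this, leave the wording unchanged for the men concerned and add a sensitivity analysis of craving that excludes those whose only qualifying substance is alcohol. The qualifying test precedes inclusion, so the exclusion does not depend on treatment. Refusal of a test also counts as positive, so say in advance how men who qualified only by refusal are classified.

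Cost: one wording change or one printed sentence. Scores move slightly further from the published alcohol version, and the sensitivity analysis has fewer men (at an assumed 30%, about 25 × 0.70 = 17.5 per arm).

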#### Instrument for Forensic Treatment Evaluation

The Instrument for Forensic Treatment Evaluation (IFTE) is an observational treatment evaluation instrument consisting of 22 items measuring 3 factors: Problematic behavior, protective behavior, and resocialization skills. It is scored on a 17-point Likert scale with 5 anchor points: none, rarely, sometimes, often, and always [47]. The IFTE assesses forensic risk behaviors such as impulsivity, hostility, and violating treatment conditions. These risk behaviors might be manifestations of impulsive behavior and could help assess engagement in impulsive behavior that is not assessed by the BIS-11 and the cued go/no-go task. Furthermore, the IFTE also assesses cooperation with treatment, which measures the amount of effort a patient puts in to make progress in his treatment, giving an indication of the degree of commitment (and thereby, motivation) of a patient to forensic treatment. The IFTE is scored twice a year by clinicians involved in patients’ treatment as part of routine outcome measurement within the treatment facility. Patients also score the IFTE on a self-report version of the original IFTE (IFTE-SR), where they can give an indication of treatment progress during the past 6 months. Scores of the IFTE and IFTE-SR are assessed from the moment a patient arrives at the treatment facility up until release. Therefore, scores on the IFTE are available throughout the research. Relevant scores included in this study will be assessments 6 months prior to inclusion up until 12 months after the last measurement.

#### Actual Drug Use

Drug testing is performed on a regular basis, usually once every 2 weeks. Whenever staff suspects illegal use of substances within 2 moments of drug testing, spontaneous and unexpected drug testing can be performed. Number of drug tests will be counted, as will be positive (meaning drug use in the period of time since last drug test) and negative (meaning no drug use since last testing) outcome scores. Drug testing is done in the form of urine, saliva, or breathalyzer (for alcohol use only) analysis.

#### Covariates

Covariates are sociodemographic characteristics; specific psychopathology; duration of forensic treatment; actual drug use during the past 24 months (or as long as patients reside in the treatment facility); medication use; clinical risk assessment score (Historical/Clinical/Future-Revised, HKT-R) [48]; actual drug use; and mean score of delta, theta, alpha, beta, and gamma resting state EEG frequency band power. Covariates will be collected through case file information. Medication and medication change will be categorized according to class of medication (eg, benzodiazepines, antipsychotic medication).

### Intervention

All participants already receive TAU at the moment of inclusion. They will continue to do so during the course of this trial. Type of TAU is dependent on disorder and behavior but can range from cognitive behavioral therapy, psychotherapy, and psychomotor therapy to relapse prevention treatment and can be either individual treatment or in-group treatment. Treatment can also be supplemented by medication for psychotic symptoms or depressive symptoms, for example. In some rare cases, aversion or craving reducing medication is prescribed.

Participants in the intervention condition of the RCT will receive 20 neurofeedback sessions, each lasting approximately 40 minutes. EEG magnitude is measured across delta (0.5-3.5 Hz), theta (3.5-7.5 Hz), alpha (7.5-12 Hz), beta (12-20 Hz), SMR (12-15 Hz), high beta (20-32 Hz), and gamma (32-49 Hz) frequency bands. To reduce inattention and impulsivity, a conventional neurofeedback protocol will be used that consists of suppressing theta magnitude and enhancing SMR magnitude [49,50]. The aims of the neurofeedback sessions are therefore to reduce slow waves (specifically theta, 3.5-7.5 Hz, and if necessary delta, 0.5-3.5 Hz) and increase faster waves (SMR, 12-15 Hz). A maximum of 3 different frequency bands will be trained during each session. Neurofeedback training will be performed on the EEG signal recorded from electrode position Cz against a right ear mastoid reference.

For the n-of-1 design of the trial, 2 participants will receive the SMR-neurofeedback intervention and 2 participants will receive sham neurofeedback.

Real and sham neurofeedback procedures will be similar (eg, electrode position, preparation, instructions given to participants) except that for the sham neurofeedback training group, participants are instructed to enhance an irrelevant frequency band that is randomly chosen from higher beta bands (20-23 Hz, 23-26 Hz, 26-29 Hz, and 29-32 Hz). Therefore, no specific frequency band is systematically modulated and thus should not result in desired treatment outcomes. Participants will still be given positive feedback and be able to influence the video games in order to minimize possible irritation of participants.

Neurofeedback will be applied as implemented within the BrainMarker software engine (BrainMarker Device, Brainmarker BV Gulpen).

Participants will be shown simple video games implemented in the software that will provide feedback about their brain activity. During the video games, they are instructed to be attentive to the feedback (no movement/movement of objects) in the video game and to find the most successful strategy to reach the goal of the game. Example of such video games are a car moving on a road, where participants are instructed to keep the car in the right lane of the road, or a basketball court where participants are instructed to try to throw the ball in the basket. The video game–based neurofeedback rounds will last 1 minute at a time, with a short break between rounds. Also, movie-based neurofeedback will be applied. During movie-based neurofeedback participants will watch a digital video disk of their own choice and be instructed to keep the monitor as free as possible from black curtains appearing on both sides of the monitor and keep the volume of the movie at an audible level. Movie-based training will last 90 seconds at a time with a short break when necessary. Participants will receive both game- and movie-based neurofeedback in each session.

Thresholds will be set manually in a way that if a participant maintains the reinforced frequency band above a threshold for 80% of time, positive feedback will be received. To determine threshold values, mean magnitude of the baseline measurement across the 3 conditions described above will be used to roughly assess threshold values for the neurofeedback training. For each training session, mean magnitude values will be calculated for all frequencies.

### Statistical Analysis

All statistical analysis will be conducted using SPSS version 19 (IBM Corp). Summarizing descriptive statistics and frequency tables will be provided.

#### Randomized Controlled Trial

Resting state EEG data will be analyzed using custom-made Matlab R2012b scripts [51]. A repeated measures multivariate analysis of variance with factors condition (neurofeedback vs control) and frequency band (delta, theta, alpha, beta, or gamma) will be conducted. If main or interaction effects are observed, post hoc tests will be used to determine which levels of the factors are explaining the observed effects.

Repeated measurement with time (pre- [T0] and postintervention [T1]) as the within-subject factor and group (control vs intervention) as the between-subject factor will be conducted for the DAQ-SF, BIS-11, IFTE, and IFTE-SR. If main or interaction effects are observed, post hoc test will be used to determine which levels of the factors are explaining the observed effects. A repeated measures analysis of covariance will be conducted to examine differences in actual drug use as dependent variables to test for a moderating effect of impulsivity on craving and actual drug use.

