### Randomized Controlled Trial

A randomized controlled trial with N=50, where 25 participants are randomly assigned to treatment as usual (TAU) combined with 20 SMR-based neurofeedback sessions and 25 participants are randomly assigned to TAU only, without neurofeedback intervention. The 2 groups are compared pretreatment (T0) and posttreatment (T1) on variables linked to the research questions. Both groups will receive pre- and posttreatment measurements with an interval between T0 and T1 of approximately 10 weeks in which participants in the intervention group will receive 20 neurofeedback treatment sessions and participants in the control condition will follow TAU.

The design of this part of the study is a 2×2 design with the condition (neurofeedback vs TAU) as a between-subjects factor and time as a within-subjects factor (pre- and postintervention).

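### The resting-state EEG model names no time factor and no separate SMR band, so as written it does not test EEG change and gives SMR no controlled test of its own

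*Protocol article*

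**What the plan says.** - **Outcome.** The Objectives section lists "changes in resting state EEG pattern" among the primary outcome variables.
- **Design.** The Randomized Controlled Trial section under Methods describes a 2x2 layout with "condition (neurofeedback vs TAU) as a between-subjects factor and time as a within-subjects factor (pre- and postintervention" measurement).
- **Data.** The Electroencephalography section states: "EEG measures will be conducted at T0 and T1 as well as at 12 months follow-up for participants in the intervention group (T2"). Both arms therefore have T0 and T1 resting recordings from 19 scalp positions.
- **EEG model.** The Randomized Controlled Trial section under Statistical Analysis specifies a repeated measures MANOVA "with factors condition (neurofeedback vs control) and frequency band (delta, theta, alpha, beta, or gamma) will be conducted". Any main or interaction effect leads to post hoc tests.
- **Questionnaire model.** The next paragraph of that section is explicit for the DAQ-SF, BIS-11, IFTE and IFTE-SR: "Repeated measurement with time (pre- [T0] and postintervention [T1]) as the within-subject factor and group (control vs intervention) as the between-subject factor".
- **Training targets.** The Intervention section describes "suppressing theta magnitude and enhancing SMR magnitude", with delta reduced if necessary. It defines SMR as 12-15 Hz, separately from beta at 12-20 Hz.
- **Second EEG source.** "For participants in the neurofeedback group, a 1-minute baseline recording over 3 conditions will be conducted" before the first and after the last session, at Cz. Its purposes include assessing change in band magnitude. The control arm has no such recording.

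**The concern.** The outcome is a change, but the only factors named for its analysis are condition and frequency band. Those yield three terms: condition, band, and condition x band. None contains time, so none compares the arms on the T0-T1 difference. A significant band effect would show only that bands differ in power, yet it too would trigger post hoc tests.

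The band list has a second gap. The intervention is named after SMR, but SMR is neither a level of the band factor nor among the EEG bands in the Covariates section. In the randomised comparison an SMR response can show only through the wider beta band. The recordings matched to the training site exist in one arm only and cannot separate training from the passage of time.

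At stake is a listed primary outcome. There is also a choice (T0 and T1 pooled, T1 alone, or change) that the text leaves open until results are seen.

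**Working it through.** **1. The plan's own figure.** The protocol gives no EEG-specific calculation. Its 21 per arm reproduces from a two-sample t-test with a standardised difference of 0.80 and one-sided 5% alpha (power 0.817). That fits 0.80 read as a mean difference in SD units, although it is labelled *f*; the label is a separate matter. I carry forward 0.80 SD and the planned 25 per arm.

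**2. What omitting time could cost.** Take one band with unit SD at each visit, no arm difference at T0 and 0.8 SD at T1. The T0-T1 correlation rho is not in the protocol; I assume 0.5 to 0.9. Power is from the noncentral t with 48 df and noncentrality d x sqrt(25/2), two-sided 5%.

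- T0 and T1 pooled: d = (0.8/2) / sqrt((1 + rho)/2). At rho 0.7, 0.4/sqrt(0.85) = 0.434.
- T1 only: d = 0.8.
- Condition x time: d = 0.8 / sqrt(2(1 - rho)). At rho 0.7, 0.8/sqrt(0.6) = 1.033.
- T1 adjusted for T0: d = 0.8 / sqrt(1 - rho^2). At rho 0.7, 0.8/sqrt(0.51) = 1.120.

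| rho | Pooled | T1 only | Condition x time | T1 adjusted for T0 |
|---|---|---|---|---|
| 0.5 | 0.36 | 0.79 | 0.79 | 0.89 |
| 0.7 | 0.32 | 0.79 | 0.95 | 0.97 |
| 0.9 | 0.30 | 0.79 | >0.99 | >0.99 |

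The sample-size paragraph uses a one-tailed 5% level. On that basis, at rho 0.7, pooled is 0.45, T1 only 0.87 and condition x time 0.98. The ordering is the same.

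**3. What reading SMR through beta could cost.** I assume the resting analysis uses the band limits in the Intervention section. SMR then covers 3 of beta's 8 Hz. Suppose only SMR moves, by 0.8 SD. Treat beta as a weighted mean of the 12-15 Hz and 15-20 Hz parts (weights 3/8 and 5/8), with equal variances and correlation r between the parts:

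d(beta) = 0.8 x (3/8) / sqrt((3/8)^2 + (5/8)^2 + 2 x (3/8) x (5/8) x r)

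- r = 0: 0.30/0.729 = 0.41, power 0.30
- r = 0.5: 0.30/0.875 = 0.34, power 0.22
- r = 1: 0.30/1 = 0.30, power 0.18

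The same difference measured in SMR itself has power 0.79 (25 per arm, two-sided, single comparison). The weights and equal variances are assumptions; if the 12-15 Hz part contributes more to beta, the dilution is smaller.

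**The case against.** The best defence is that time is implied. The design section makes time a factor of the whole RCT, EEG is recorded at both visits in both arms, and the model is called repeated measures. The article is also a condensed account. This makes an intended time factor plausible but does not put one in the model. Frequency band already supplies the repeated measure, and the adjacent paragraph spells out time and its levels for the questionnaires. The article gives factors for both models, and they differ.

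Three stronger readings are tempting, and the document supports none of them:

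- *The analysis cannot tell whether neurofeedback moved its target.* There are two main targets. Theta is a listed level, as is delta, so adding time alone gives a controlled test of theta. SMR is present in beta, though diluted.
- *The trial cannot show an EEG effect against TAU.* Both arms have the T0 and T1 recordings. The weakness lies in the stated model, not in the data.
- *Power falls to about 0.32.* That holds only if the visits are pooled, which the text does not say. With T1 alone the randomised comparison is valid at 0.79, and at rho 0.5 it equals the change test; it still does not analyse change.

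It is also fair that neither the primary objective nor the three secondary objectives mention EEG. The n-of-1 trials and the per-session magnitudes give further evidence on the trained bands. They limit the consequence, but they do not replace a controlled contrast for an outcome listed as primary.

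**Conclusion.** The point holds in two parts. First, the EEG model as written has no condition x time term, so it does not test the listed primary outcome and departs from the protocol's own 2x2 design. Second, SMR has no separate level, so no controlled test of SMR change is planned. Both statements rest on the text alone.

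The size is illustrative. It depends on which data enter the model and on an assumed T0-T1 correlation, and ranges from a large loss of power (pooled) to none (T1 alone at rho 0.5). The SMR dilution, from 0.80 to between 0.41 and 0.30 SD, rests on the band-weight and variance assumptions above. This goes beyond missing detail, because the factors are stated and do not match the outcome. It can be repaired fully before analysis.

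**What to change.** 1. Add time (T0, T1) to the EEG model, giving condition x time x band, or analyse T1 band power adjusted for T0. Name one as the planned test.
2. Add SMR (12-15 Hz) as a band, computed from the resting recordings already made in both arms. Because it lies inside beta (12-20 Hz), state how the overlap is handled, for example by analysing bands separately or limiting the beta level to 15-20 Hz.
3. Base the treatment conclusion only on terms containing condition x time, or on the baseline-adjusted arm effect. Let only these trigger post hoc tests, corrected for the number of bands.
4. Report the neurofeedback-only Cz recordings as uncontrolled and descriptive.

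Log-transforming power or restricting the test to Cz are reasonable choices, but the repair does not need them. The cost is a revised analysis paragraph and one more band in the existing Matlab scripts, with no new measurements and no change in sample size. The change should be made and dated before the arms are compared on EEG.
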